In an Ethiopian study of HIV-1 infected and uninfected individuals, helminth infections resulted in increased memory CD4 cells and increased T-cell activation, and treatment of helminth infections was associated with decreased T-cell activation. Interestingly, among the HIV-1 infected individuals in this observational study, treatment of helminth infection resulted in a significant increase in absolute CD4 counts (192 versus 279 cells/mm^3,  $p=0.002$ ). In another study of 56 HIV-1 infected individuals in Ethiopia, 31 (55%) had helminth co-infections with one or more species detected in stool samples, mainly *Ascaris lumbricoides* and *Trichuris trichiura*. At baseline, there was a strong association between stool helminth burden and plasma HIV-1 RNA levels among individuals with helminth co-infection ( $p<0.001$ ). In addition, successful treatment of co-infection (as documented by clearance of helminth eggs in stool) led to a significant decrease in HIV-1 plasma viral load ( $-0.36 \log_{10}$ ) in these patients. This change in viral load was significantly greater than that seen in those individuals without documented clearance of their helminth co-infection ( $+0.67 \log_{10}$ ) ( $p=0.04$ ). Other studies suggest that this effect may be variable, depending both on the type and duration of helminth co-infection as well as on host immune status. In one such study from Kenya, plasma HIV-1 RNA levels did not decrease significantly following treatment of schistosomiasis.

The majority of HIV-1 infected individuals do not yet meet criteria for HAART. These individuals continue to transmit the virus and perpetuate the epidemic. For each log increase in plasma HIV-1 viral load, there is an estimated 2.5-fold increased risk for transmission to the sexual partner of the infected individual. Thus, the benefit of reducing viral load by even 0.5 log could be substantial. Identifying inexpensive and feasible interventions that may reduce viral load has the potential for significant public health benefit.

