### **Justification of the Study:**

To date, there are no randomized clinical trials evaluating the effect of anti-helminth treatment on immune activation, CD4 count, and HIV-1 viral levels. It is important to determine whether routine treatment of helminth co-infection should be considered standard practice in the treatment of HIV-1 infected individuals in helminth endemic areas. Such treatment may be a useful strategy to delay HIV-1 progression and prevent transmission of HIV-1 among individuals in resource-poor settings. Interval anti-helminth therapy may be a feasible option in many areas of the world to delay immunosuppression, to enhance the response to antiretroviral therapy or to reduce infectiousness in HIV-1 infected individuals. In addition, as patients progress to HAART, it is important to determine the ideal timing for helminth eradication.

**Hypothesis:** Treatment of gastrointestinal helminths in patients with HIV-1 may impact markers of disease progression and infectiousness, namely CD4 count and plasma and genital HIV-1 RNA levels, when compared to no treatment in these individuals.

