### **Specific Objectives:**

1. To determine prevalence and correlates of helminth co-infection in HIV-1 infected individuals in various clinics in or around Nairobi, Kenya. Baseline demographic, socio-economic and geographic data such as age, gender, income, education, occupation and place of residence will be collected and compared to determine what factors influence the prevalence of helminth infection in patients with HIV-1.
2. To determine if treatment of intestinal helminths in HIV-1 infected adults can delay disease progression, as measured by CD4 counts and HIV-1 RNA viral loads.
3. To determine if treatment of intestinal helminths in HIV-1 infected adults can reduce shedding of genital HIV-1 and impact transmission.

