b) *Clinical trial*: HIV-1 infected helminth co-infected individuals who elect to participate in the randomized clinical trial will be enrolled following written informed consent. Those patients who are enrolled in the treatment phase will have blood collected for baseline plasma HIV-1 RNA levels and CD4 cells. Computer-generated random number allocation will be used to assign treatment group. The pharmacy at the clinic will be responsible for the determination of randomization group and distribution of albendazole and placebo. The pharmacy will also be responsible for maintaining records regarding treatment group. Treatment will be provided in the form of three 400 mg pills of albendazole or a three placebo pills identical in appearance (to be taken one pill per day for each of three consecutive days). Both placebo and albendazole will be provided in an identical appearing envelope. Treatment arms will consist of either initial therapy with albendazole (400 mg a day for three days) or an initial three days of placebo pills. All patients will be required to visit the clinic eight weeks after enrollment. At this twelve-week visit, stool samples will again be collected for evaluation of helminth infection. Plasma CD4 count and HIV-1 RNA level measurements will be repeated at this twelve-week visit. All patients who received placebo initially as well as all patients with evidence of helminth infection will be treated with open-label albendazole therapy regardless of initial treatment arm.

At enrollment and the twelve-week visit, lymphocytes will also be isolated from serum samples for assessment of immune activation markers. Genital HIV-1 RNA levels will be compared in 100 individuals randomized to immediate versus deferred antihelminthics at baseline and at the 3-month visit (prior to receiving deferred therapy). This will provide data quantifying the potential effect of anti-helminthic treatment on genital HIV-1 RNA. Consenting adults will have genital swabs collected (semen or cervical/vaginal) and placed in freezing media prior to cryopreservation and transport to Fred Hutchinson Cancer Research Center for HIV-1 RNA assays.

Patients who do not follow-up as directed will be contacted by the administrative support team at their homes in order to determine the reason for each loss to follow-up. Any adverse events during the treatment period will be reported and managed accordingly at the treatment clinic.

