### *Data Management*

*Data Entry and Storage:* All data will be collected on preprinted forms that are able to be scanned directly or data entered into a software data management program (Teleform SPSS or ACCESS). Data will be collected at enrollment and at each follow up visit on these forms. Following collection, the data forms will be scanned into the database as described above. Original data forms will be stored in the study offices with access restricted to study investigators. Following completion of all data collection, the data forms will be archived. At 1-year following completion of the study, identifiers will be removed from the data. Data will be the property of KEMRI and the University of Washington.

*Data verification:* A data clerk from KEMRI will be employed to hand verify that all data is completed accurately and that the computerized scanned data is comparable to the paper forms. Data will be cleaned by the Fellow Investigator and the data clerk and at that time a second verification of accuracy will be performed.

*Data Analysis:*

**Aim 1:** Prevalence of helminth co-infection will be determined in the total screened population by individual, by clinic and by cohort. To determine correlates of helminth co-infection, mean CD4 count, age and log10 RNA levels will be compared in individuals with and without helminth co-infections using t-tests. Dichotomous variables (socio-demographic) will be compared with Chi square tests in individuals with and without helminth co-infection. Similar analyses will be conducted to determine correlates of re-infection and eradication.

**Aim 2:** All analyses will be intent-to-treat. To assess the success of randomization we will compare baseline characteristics between the 2 randomization groups. To determine the effect of antihelminth treatment on disease progression markers, we will compare month one measurements of mean CD4 count, log10 plasma HIV-1 RNA, and percentage of cells with specified immune activation markers in the 2 study arms using t-tests or non-parametric testing. In addition, prevalence of helminth co-infection will be compared in the 2 study arms using Chi-square tests. To determine the effect of antihelminth treatment on infectivity, we will compare enrollment measurements of mean genital HIV-1 RNA levels with the 12 week follow up measurements.

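### The Data Analysis text fixes genital HIV-1 RNA as an enrolment-versus-12-week comparison with no reference to arm, contradicting the randomised comparison described elsewhere in the protocol

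*Protocol*

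**What the plan says.** The objective and hypothesis are causal and comparative. Specific Objective 3 is "To determine if treatment of intestinal helminths in HIV-1 infected adults can reduce shedding of genital HIV-1 and impact transmission". The hypothesis, under Justification of the Study, covers three markers, "namely CD4 count and plasma and genital HIV-1 RNA levels, when compared to no treatment in these individuals".

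The Clinical Trial section, item b, sets out the genital sub-study: "Genital HIV-1 RNA levels will be compared in 100 individuals randomized to immediate versus deferred antihelminthics at baseline and at the 3-month visit". It adds that the second sample is taken before deferred therapy is given, and that the purpose is to quantify the effect of treatment on genital RNA.

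Data Analysis, Aim 2, opens with "All analyses will be intent-to-treat". It then compares CD4 count, plasma HIV-1 RNA and "percentage of cells with specified immune activation markers in the 2 study arms using t-tests or non-parametric testing", and compares helminth prevalence by arm as well. The last sentence of the paragraph deals with genital RNA. Its purpose is "To determine the effect of antihelminth treatment on infectivity", and its method is "we will compare enrollment measurements of mean genital HIV-1 RNA levels with the 12 week follow up measurements". No arm and no test are named. This is the only analysis statement for genital RNA in the protocol.

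**The concern.** The sentence claims a treatment effect but contrasts two time points. A before-after difference contains whatever would have happened over 12 weeks without treatment: natural change in shedding, changes in assay or sample handling, and other influences that vary with time. The trial has a concurrent, untreated, randomised control at the follow-up visit precisely to remove these, and the written analysis does not use it.

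At stake is the only stated analysis for one of the three specific objectives. An analyst who followed the sentence could report ordinary drift as a treatment effect, or miss a real effect because drift ran against it.

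**Working it through.** **1. Is there a plan figure to reproduce?** No. The Sample Size section concerns CD4 count only. For genital RNA the protocol gives 100 participants but no effect size, SD or power, so the point rests on the contrast and not on a sample size.

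**2. The passages side by side.**

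| Place in protocol | Contrast for genital RNA |
|---|---|
| Justification of the Study, hypothesis | Treatment against no treatment |
| Clinical Trial, item b | Immediate against deferred, at baseline and month 3, deferred arm still untreated |
| Data Analysis, Aim 2, other markers | Between the two arms |
| Data Analysis, Aim 2, genital RNA | Enrolment against 12 weeks, no arm named |

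The first three rows agree and the fourth does not. Taking the second sample before deferred therapy matters only if the deferred arm serves as an untreated comparison.

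**3. What each contrast estimates.** Let *d* be the mean 12-week change without treatment and *e* the added effect of assignment to immediate treatment.

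- Treated arm only, before-after: *d* + *e*
- Both arms pooled 1:1, before-after: *d* + *e*/2
- Between arms: (*d* + *e*) − *d* = *e*

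Only the third isolates *e*. The 1:1 split of the 100 is an assumption.

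**4. False-positive rate when *e* = 0.** For a two-sided 5% paired test, normal approximation, with x = *d*/(SD of change/√n):

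P(significant) = 1 − Φ(1.96 − x) + Φ(−1.96 − x)

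Drift and SD of change are assumed, since the documents give neither.

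| Drift (log10) | SD of change (log10) | Pooled, n = 100 | Treated arm only, n = 50 |
|---|---|---|---|
| 0 | any | 5% | 5% |
| 0.1 | 0.6 | 38.5% | 21.8% |
| 0.1 | 0.8 | 24.0% | 14.3% |
| 0.1 | 1.0 | 17.0% | 10.9% |
| 0.2 | 0.6 | 91.5% | 65.4% |
| 0.2 | 0.8 | 70.5% | 42.4% |
| 0.2 | 1.0 | 51.6% | 29.3% |

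**5. Illustration with figures in the protocol.** The Introduction cites plasma changes of −0.36 log10 with documented clearance and +0.67 log10 without. These are plasma values grouped by clearance in a non-randomised comparison, so they are not arm means. To approximate arms, take the 67% cure rate quoted for the three-day regimen under Ethical Considerations, Risks. Assume no clearance on placebo, and assume genital RNA follows the plasma pattern.

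- Treated arm: 0.67 × (−0.36) + 0.33 × (+0.67) = −0.241 + 0.221 = −0.02 log10
- Placebo arm: +0.67 log10
- Between arms: −0.02 − 0.67 = −0.69 log10
- Pooled 50:50: (−0.02 + 0.67)/2 = +0.325 log10

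On these assumptions a treated-arm before-after analysis shows almost no change and a pooled one shows a rise, while the arms differ by 0.69 log10 in favour of treatment.

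**6. Is the randomised comparison workable?** With 50 against 50 (assumed), 80% power and two-sided 5%, the detectable difference is (1.960 + 0.842) × √(2/50) = 0.56 SD. The Introduction regards a 0.5 log reduction in viral load as potentially substantial. Power for 0.5 log10, without baseline adjustment:

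| Assumed SD (log10) | Detectable difference (log10) | Power for 0.5 log10 |
|---|---|---|
| 0.6 | 0.34 | 99% |
| 0.8 | 0.45 | 88% |
| 1.0 | 0.56 | 71% |
| 1.2 | 0.67 | 55% |

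**The case against.** The strongest reply is that the randomised contrast is already in the protocol. The Clinical Trial section states it, the hypothesis implies it, the neighbouring analyses are by arm, and everything is declared intent-to-treat. On that view the genital sentence merely leaves out a phrase, and a sensible analyst would compare the enrolment-to-12-week change by arm.

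Much of this stands. The defect is confined to one sentence. Pooling over arms is one possible reading of it; the sentence says neither that arms are pooled nor that only the treated arm is used.

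It does not dispose of the point. Intent-to-treat settles how participants are classified; it does not turn a comparison of two time points into a comparison of arms. Nor is this detail left for a statistical analysis plan: the protocol states a contrast, and that contrast disagrees with its own procedures.

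Two further readings go beyond the text. A reader might infer that semen, cervical and vaginal results are to be combined in a single mean. The protocol says which specimens are collected but not that they are combined, and handling by specimen type may properly be left to an analysis plan. A reader might also take −0.36 and +0.67 log10 as the expected changes on albendazole and placebo, giving a contrast of −1.03. Those groups were defined by documented clearance, and the protocol's own cure figure shows that assignment and clearance differ.

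**Conclusion.** The point holds as an internal contradiction in which the Data Analysis section carries the wrong contrast. As written, the genital RNA analysis cannot separate treatment from time trend, and it would dilute the effect as well if arms were pooled.

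A reader might conclude that the trial cannot address Objective 3. The documents do not support that. The limitation belongs to the stated analysis; the design provides an untreated randomised control at the follow-up sample, and the planned data allow the right comparison. Regression to the mean adds little here, because participants are not selected on genital RNA.

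The direction of the problem needs no outside figure; its size does. The false-positive rates depend on assumed drift and SD of change, and the nominal 5% holds only at zero drift. The −0.02, −0.69 and +0.325 log10 figures are illustrative and rest on the assumptions in step 5. Because this is the sole analysis sentence for a specific objective, it should be corrected before the data are analysed.

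**What to change.** Replace the genital RNA sentence under Aim 2 with a comparison of 12-week log10 genital HIV-1 RNA between the immediate and deferred arms, by assigned arm, matching the Clinical Trial section.

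Preferably, adjust for the baseline genital RNA already being collected and for specimen type. The Risks text allows a woman to give vaginal and/or cervical samples, so either pre-specify one specimen per participant or use a method that allows for repeated specimens from the same person. Report within-arm changes as description only.

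The between-arm contrast is the essential correction; the adjustments are refinements. If a separate analysis plan exists, it should carry the same wording. The cost is a protocol wording change: both arms and both visits are already planned, and no added samples or participants are needed.

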**Time Schedule**

Total period of project is 12 months

We anticipate a 2-month preparation period followed by 7 months of recruitment and follow-up. Laboratory and data analysis will take 2 months and manuscript preparation will take 1 month.

**Ethical Considerations:**

**Ethical approval- Study approvals will be obtained from the University of Washington and the KEMRI ethical review boards.**

*Benefits:* This study has been designed to address several areas of major public health significance for HIV-1 infected individuals in resource poor settings. If we are able to show that treatment of helminth co-infection in HIV-1 infected individuals delays immunosuppression, millions of HIV infected individuals in resource poor settings may benefit. Clients who have helminth infections will benefit from free treatment and examination given to them.

*Voluntary Participation:* All subjects will provide written informed consent prior to study enrolment. Consent forms will be made available in Swahili as well as in English. All patients will have the opportunity to have the forms explained to them and to ask questions of the investigator prior to study enrolment. Patients will be informed of their right to withdraw consent at any time. Since the participants will spend extra time to participate in the study, they will receive compensation for transport, but no other compensation will be provided to them.

*Risks:* Patients will be informed of all potential risks. The first risk may be associated with use of the study medication, albendazole. Albendazole is a benzimidazole carbamate derivative with activity against most nematodes and some other worms. Albendazole is thought to inhibit cytoplasmic microtubules in the worm's intestinal tract leading to decreased glucose uptake and depletion of glycogen stores in the worm. Three 400 mg doses of albendazole has efficacy against whipworm, hookworm and roundworm infections, all of

which we expect to be prevalent in this cohort. A recent randomized controlled trial of various albendazole dosing regimens showed that a single 400mg dose of albendazole was associated with a significantly lower rate of cure (23%) compared to a three day regimen (67%). In this study, reduction in the number of eggs/gm of feces with a single 400mg dose was 96.8% compared to 99.7% with the three day regimen. Albendazole is minimally absorbed from the gastrointestinal tract and has minimal side-effects. Patients will be screened for helminth infection at enrolment and subsequently randomized to immediate versus deferred (twelve weeks later) treatment of intestinal helminth infection. Patients with obvious clinical signs or symptoms of anaemia, significant diarrhoea or abdominal pain will not be enrolled. A twelve week treatment delay in those patients who are asymptotically infected but do not receive active drug is not anticipated to have any adverse health consequences. Neither routine screening of asymptomatic helminth infection nor empiric anti-helminth therapy is currently conducted in adults in Kenya. Patients will have blood withdrawals at enrolment and during follow-up. This may be associated with bleeding or swelling at the injection site. Precautions will be taken to avoid bleeding by immediate application of a pack and pressure at the injection sites.

A subset of participants (100 individuals) will be included in the study of genital HIV-1 RNA levels. This will require collection of a semen sample from male participants and collection of vaginal and/or cervical samples from female participants. Participants may find this embarrassing. Female participants will undergo a pelvic examination for collection which may be uncomfortable.

*Confidentiality:* Patients will be assigned a study number at enrollment. This number will be used to identify patients for all matters related to data analysis. The forms linking patient names and demographic information to particular ID numbers will be kept locked in a file at the office of the Fellow Investigator.

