#### *Exclusion Criteria*

- Participants who have received treatment for helminth infection in the past 6 months (by self report or chart review)
- Participants must not be pregnant at the time of treatment (by urine HCG testing).
- Participants who present with other serious co-morbidities such as severe anaemia, malaria or tuberculosis

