### Clinical Trial:

a) Screening for trial eligibility: At the selected clinical trial study site, HIV-1 infected individuals who meet inclusion and exclusion criteria will be informed about screening for stool helminths. A physical examination will be conducted on all prospective clients, and those found to have clinical pallor, or signs and symptoms of tuberculosis, malaria or malignancy will be excluded from the study and referred for appropriate medical management. Individuals with CD4 counts >250 cells/mm^3 will be eligible for study screening following written informed consent for study screening. For those individuals without available CD4 count data, patients will be screened if there is no evidence of WHO Stage II-IV disease. Patients who are subsequently found to have CD4 counts less than 250 cells/mm^3 will be referred for further HIV care at the referring clinic. The individual clinic sites will be notified of all CD4 count results within 14 days of testing. Baseline demographic and socio-economic data will be collected from these patients using standardized questionnaires. Stool samples will be collected and evaluated for ova and parasites. Participants who are found to have positive stool parasite examinations will be

informed about the clinical trial and those who consent to participate will be enrolled in the treatment phase of the study. Those who are found to be infected with helminths but who decline to participate in the treatment phase will be treated at no charge with a three day course of 400mg/day of albendazole by the study investigators. Those who are found to have negative stool specimens will not continue to the treatment phase. After screening exit (either due to lack of helminths or declining to participate), individuals will be referred back to the clinic in which they receive their usual care.

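### Significant diarrhoea and abdominal pain bar enrolment in the Risks text but are missing from the eligibility criteria and screening steps, although the argument for a twelve-week delay is made for people without symptoms

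*Protocol*

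**What the plan says.** Three places in the Protocol say who is kept out on clinical grounds.

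- Ethical Considerations, Risks: "Patients with obvious clinical signs or symptoms of anaemia, significant diarrhoea or abdominal pain will not be enrolled".
- Exclusion Criteria: "Participants who present with other serious co-morbidities such as severe anaemia, malaria or tuberculosis". The other two entries in that list concern anti-helminth treatment in the previous six months and pregnancy.
- Clinical Trial, part a (screening): after a physical examination of everyone considered, "those found to have clinical pallor, or signs and symptoms of tuberculosis, malaria or malignancy will be excluded from the study".

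The Risks paragraph follows its restriction with the argument for the placebo arm: "A twelve week treatment delay in those patients who are asymptotically infected but do not receive active drug is not anticipated to have any adverse" effect on health. The adverb is evidently meant to be the one for infection without symptoms. It then adds a point about usual practice: "Neither routine screening of asymptomatic helminth infection nor empiric anti-helminth therapy is currently conducted in adults in Kenya".

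Study Populations refers the reader to the Inclusion and Exclusion Criteria for eligibility. The Inclusion Criteria do not require freedom from symptoms. Under Clinical Trial, entry to the randomised phase follows from a positive stool result and consent.

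**The concern.** The Risks paragraph tells an ethics board two linked things: people with marked symptoms are kept out, and for the remainder a twelve-week wait is acceptable. The second statement depends largely on the first. If the first is not built into the steps by which people are screened and enrolled, the trial may admit people for whom the Protocol has not justified the wait.

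Two things are at stake. One is participant protection: a symptomatic person allocated to placebo waits twelve weeks for open-label drug, whereas a helminth-positive person who declines the trial is treated free of charge at once. The other is the population the results describe. Whether the CD4 and viral-load comparison concerns people with asymptomatic infection only, or a mixture, would depend on which section each screener happened to follow.

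**Working it through.** No arithmetic applies to the main point, and the Protocol gives no figure to reproduce. The check is to trace each condition in the Risks paragraph through the sections that decide enrolment.

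| Condition | Risks | Inclusion Criteria | Exclusion Criteria | Clinical Trial, a (screening) | Clinical Trial, b (enrolment) |
|---|---|---|---|---|---|
| Anaemia | Obvious signs or symptoms | – | Severe anaemia, as an example | Pallor | – |
| Diarrhoea | Significant | – | – | – | – |
| Abdominal pain | Named | – | – | – | – |
| Malaria, tuberculosis | – | – | Named, as examples | Signs and symptoms | – |
| Malignancy | – | – | – | Signs and symptoms | – |

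Step 1. Of the three conditions in the Risks paragraph, one (anaemia) has a counterpart in the operative sections. Two (significant diarrhoea, abdominal pain) have none.

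Step 2. Could the open wording of the co-morbidity criterion cover the two missing conditions? It gives examples, so it is not closed, but what it leaves open is the class of serious co-morbidities. Diarrhoea or abdominal pain caused by the helminth infection under study is not clearly a co-morbidity, and need not be serious in that sense.

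Step 3. Does another step catch these people? The physical examination could, but the findings for which it excludes are listed and these two are not among them. The questionnaires named at screening collect demographic and socio-economic data. A positive stool result and consent then lead to enrolment.

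Step 4. Anaemia. No passage gives a haemoglobin cut-off. Pallor and obvious clinical signs are close in substance. Only the Exclusion Criteria are narrower, and a person with pallor is excluded at the examination in any case. The difference in wording needs tidying but is the smaller part of the problem.

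Step 5. Size. Sample Size plans 100 people per arm, 200 in all. If k symptomatic people were randomised, about k × 100/200 = k/2 would be expected in the deferred arm. The Protocol gives nothing from which to estimate k. The figure of 100 deferred participants bounds the number exposed and does not estimate it.

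**The case against.** The strongest reply is that this is an omission and not a conflict. The Risks paragraph is part of the same Protocol and its wording is unconditional. No passage permits enrolling someone with significant diarrhoea or abdominal pain. The three lists can be applied together, with a person excluded if any one of them applies, and the physical examination gives an occasion to do so. All of this is correct. It means the restriction is missing from the operative sections, not from the Protocol. It does not dispose of the point, because Study Populations directs staff to the Inclusion and Exclusion Criteria, and a screening form built from those and from the screening text would omit the two conditions.

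A second reply is that the safety argument has another support. In the sentence on usual practice, the word for infection without symptoms qualifies routine screening; the statement about empiric therapy is not limited in that way. This stands: the exclusion is a main support for the delay but not the only one.

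A reader might also infer more than the documents support:

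- That three different anaemia thresholds are in force. No threshold is given anywhere, and two of the three wordings nearly coincide.
- That the trial population is undefined. The Risks paragraph states the intent; it has not been carried through.
- That every helminth-positive person screened is affected, with half of them deferred. Those who decline are treated, those with CD4 counts too low for the trial are not randomised, and pilot participants away from the trial site receive open-label drug.

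**Conclusion.** The point holds as a failure to carry a stated restriction into the sections that govern enrolment. Significant diarrhoea and abdominal pain are barred in the Risks paragraph and absent from the inclusion, exclusion, screening and enrolment text. Anaemia is worded more narrowly in the Exclusion Criteria than elsewhere. A site relying on the eligibility and screening sections alone could randomise symptomatic people, some of them to deferred treatment, outside the group for which the Protocol argues that delay is acceptable.

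This rests on two assumptions: that staff build their screening from the sections labelled for that purpose, and that the co-morbidity criterion is not read to include symptoms of the helminth infection itself. The documents do not show that such people would in fact be randomised, and the number cannot be estimated from them. The matter still deserves correction before recruitment, because it concerns participant protection and the remedy is cheap.

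**What to change.** Reconcile the Exclusion Criteria, the screening text under Clinical Trial part a, and the Risks paragraph into one exclusion list, and use that list on the screening form. The restriction on which the Risks paragraph relies should then either appear in the operative criteria or be withdrawn from the safety justification, with the argument for the delay restated accordingly. Use one wording for anaemia throughout, and correct the adverb in the sentence on delay. Which conditions and what clinical threshold should apply is for the investigators to decide; this review takes no position on that.

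The cost is wording in the Protocol and on the screening form. If the wider list is kept, slightly fewer people will be eligible, which adds a little to the planned screening of roughly 600 to 2000 individuals.
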